### Post-trial care

Conventional therapy will be continued in consultation with the physicians in charge.

### Data management

#### Monitoring

A monitoring officer will conduct monitoring before, during, and after completion, termination, or withdrawal from the study.

### Harms and benefits

Potential burdens and risks

EMS is widely used in patients with cardiac disease or diabetes mellitus, and its sufficient safety has been proven. However, the adverse side effects listed below have been reported, and thus will be monitored for continuously during the study. If they do occur, the physician in charge will provide appropriate care and treatment.

#### Potential side effects

Skin injury and rash at the site of belt attachmentAggravation of pain at the site of fracturePain during EMS
2.Expected benefits

The benefits of conventional physiotherapy are already well established in rehabilitation. Also, EMS is reported to prevent muscle atrophy. Thus, addition of EMS to the conventional physiotherapy with proven benefits may enhance the therapeutic effect.

### Evaluation and reporting of adverse events

#### Definition of adverse events

Serious adverse eventsWe will record any adverse event listed below, occurring in the period between the date of providing informed consent and day 14, irrespective of the presence or absence of a causal relationship. Also, we will promptly report any occurrence to the head of the research institute via the reporting division of the hospital within 7 days after the serious adverse event is first noticed.Serious adverse events:Resulting in deathBeing life-threateningRequiring inpatient hospitalization or prolongation of existing hospitalizationResulting in persistent or significant disability/incapacityResulting in congenital anomalyOther adverse eventsThe therapeutic devices that will be used in this study have already been approved and are routinely used in the clinical setting. Thus, we will not record non-serious adverse events.We will use the designated case report form to record case information. We will register the case information digitally, with the principal investigator assigning the case number. After registration, the principal investigator and an analyst will analyze individual cases. They will pass the analysis report to the planning and strategy manager.

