### Interventions

#### Intervention group

For electrical muscle stimulation, we will use the AUTO Tens PRO Rehabili Unit B-SES (belt electrode skeletal muscle electrical stimulation; Medical Device Certification No.: 224AHBZX00015000) and G-TES (general therapeutic electrical stimulator; Medical Device Certification No.: 228AGBZX00036000) devices (both Homer Ion Co. Ltd., Tokyo, Japan). We will wrap the AUTO Tens PRO belt electrodes around the abdomen, proximal aspect of the legs, and ankles for electrical stimulation of the entire lower extremities. Patients will receive one 20-min EMS session daily, consisting of 5-s stimulations (20 Hz) separated by 2-s rest intervals, for 5 days per week for 2 weeks. The output current will be in the range 2–15 mA, and the current will be increased to the maximum tolerable level within 3 days of starting rehabilitation. A co-investigator who is a physical medicine and rehabilitation physician will supervise the 14-day EMS protocol. In parallel, we will provide conventional physiotherapy on the same day as the EMS session (also for 20 min daily). Conventional physiotherapy will consist of (1) hip and ankle joint mobility exercises and (2) lower limb-strengthening exercises in a supine position.

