#### Secondary endpoints

We will measure all secondary endpoints on the same dates that CT imaging is obtained.Change in cross-sectional area of calf muscle between pre and post intervention, as measured on CT imagesReduction in thigh and calf circumference, measured at the same sites as CT image measurementsThigh and calf circumference measured on CT imagesChanges in manual muscle testing results

We will obtain baseline CT data of the region including the pelvis and lower extremities at the time of admission (pre intervention, from day − 4 to day 0) and measure cross-sectional area of the thigh and calf muscles. Day 1 is defined as the first day of rehabilitation intervention.

To evaluate the outcomes of intervention, we will obtain post-intervention plain CT data of the region including the pelvis and lower extremities and measure cross-sectional area of the thigh and calf muscles on day 14 of intervention (or before the end of day 17). Specifically, we will obtain the following measurements.Thigh: height at the center of a line linking the greater trochanter and knee joint cleftCalf: height at the center of a line linking the fibular head and external condyleThigh and calf muscle cross-sectional area: we will extract areas with intensity in the range of 30 to 100 Hounsfield Units (HU) from CT slices and measure cross-sectional area to determine change between pre- and post-intervention values

We will obtain CT scans in the supine position with both legs in the neutral position, with a pillow placed under both legs to avoid compression of the posterior aspect of the legs from the CT bed. We will ask patients to relax to minimize the influence of morphological changes due to muscle contraction. The following CT machines will be used:Aquilion™ CX TSX-101A/NA, Application Ver. V4.62JR019 (Toshiba Medical Systems Corp., Tokyo, Japan)SOMATOM Definition Flash VA44A, Somaris/7 Syngo CT 2012BWinNT 6.1, Service Pack 1, VA44A_08_P16 (Siemens Healthcare, Forchheim, Germany)Aquilion ONE™ TSX-301A/2A, Application Ver. V4.7JR004 (Toshiba Medical Systems Corp.)Discovery CT 750HD, Application Software, 11 MW44.11.V40_PS_HD64_G_GTL (General Electric Healthcare, Waukesha, WI, USA)

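### Serious adverse events are recorded only to day 14, while the post-intervention assessment may be as late as day 17, leaving up to three days uncovered

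*Protocol article*

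**What the plan says.** Under Definition of adverse events, the protocol article records serious adverse events "occurring in the period between the date of providing informed consent and day 14", whether or not they are causally related. The same section adds: "Thus, we will not record non-serious adverse events". The seven-day reporting deadline given there sets how fast an event must be reported once noticed. It does not extend the period in which an event must occur to be counted.

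The other time points are set elsewhere in the article:

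- **Day numbering** (Secondary endpoints): "Day 1 is defined as the first day of rehabilitation intervention".
- **EMS schedule** (Intervention group): one session a day "for 5 days per week for 2 weeks", and a rehabilitation physician "will supervise the 14-day EMS protocol".
- **Post-intervention CT** (Secondary endpoints): "on day 14 of intervention (or before the end of day 17". All secondary endpoints are measured on the dates of the CT scans.
- **Last CK sample** (Participant data collection): days 14 to 17.
- **Function scores** (Participant data collection): 1 and 2 months after injury.
- **Side effects** (Harms and benefits): the listed effects are to be "monitored for continuously during the study".

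No section extends adverse-event recording beyond day 14.

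**The concern.** The recording rule ends on a day when treatment may still be given and when the outcome assessment may still be up to three days away. Followed to the letter, it leaves out a serious event that occurs after the last EMS session and before the CT that supplies the primary endpoint.

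Two things are at stake. First, the comparison of serious events between the arms may miss events that closely follow the last exposure. Second, if such an event prevents the CT, the patient loses the primary outcome and the adverse-event data need not show why. The Missing data section sets no firm rule for such patients, so the reason for a missing CT is worth having.

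The window also sits uneasily with the statement of continuous monitoring during the study, since study measurements continue to day 17 and function scores are collected later still.

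**Working it through.** The plan gives no figure to reproduce here. The check is calendar arithmetic on the stated days.

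**Inputs.** Day 1 is the first rehabilitation day. EMS is given on 5 days a week for 2 weeks, so 5 × 2 = 10 sessions in 14 days. Recording of serious adverse events closes on day 14. The assessment is permitted from day 14 to day 17.

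**Step 1: day of the tenth session.** The article does not say which days of the week are used. Assuming weekdays only:

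| Start (day 1) | Days of sessions | Tenth session | Days left in window (14 − tenth session) |
|---|---|---|---|
| Monday | 1–5, 8–12 | day 12 | 2 |
| Tuesday | 1–4, 7–11, 14 | day 14 | 0 |
| Wednesday | 1–3, 6–10, 13–14 | day 14 | 0 |
| Thursday | 1–2, 5–9, 12–14 | day 14 | 0 |
| Friday | 1, 4–8, 11–14 | day 14 | 0 |

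Without the weekday assumption, but with five sessions in each of days 1–7 and 8–14, the fifth session of the second week falls on day 12 at the earliest (8 + 4) and day 14 at the latest. The range is again 0 to 2 days.

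**Step 2: from the end of recording to the assessment.** Gap = assessment day − 14.

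| Assessment day | Uncovered days |
|---|---|
| 14 | 0 |
| 15 | 1 |
| 16 | 2 |
| 17 | 3 |

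At most, 3 of the 17 days from day 1 to the latest assessment are uncovered.

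**Step 3: does any other record cover these days?** Non-serious events are not recorded at any time. CK may be drawn up to day 17. Vital signs, level of consciousness and pain are recorded around or during EMS sessions, in the EMS group only. These data bear on safety, but none of them would document a death, a life-threatening event or a prolonged hospital stay on days 15 to 17.

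**The case against.** The strongest reply is that the window matches the 14-day EMS protocol, that day 14 is the nominal assessment day, and that days 15 to 17 are only a tolerance. For a patient assessed on day 14 there is no gap before the assessment. The listed side effects (skin injury or rash under the belt, fracture-site pain, pain during EMS) are mainly tied to application. The sample size rationale reports no dropouts, including from death, among about 25 earlier patients hospitalized for two weeks. A lost patient would not go unnoticed either: the CT would be missing, and a death should surface when the function scores fall due at 1 and 2 months.

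Most of this stands and limits the size of the point. It does not remove it. The tolerance is part of the plan, and the recording rule does not follow it. The earlier experience concerns dropouts over two weeks and gives no rate of serious events after day 14. A missing CT shows that an outcome was lost, not that a serious event caused it.

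A reader might also infer more than the documents support:

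- *That this window is the trial's only safety record, or that nothing bearing on safety is observed after the last session.* CK can be taken up to day 17, the EMS arm has vital signs and pain, and skin or striated muscle injury is a criterion for discontinuation. The window is the only adverse-event recording rule, which is a narrower statement.
- *That recording always ends before the assessment.* It does so only when the assessment falls on days 15 to 17.
- *That four fifths of patients have their last session on day 14.* Four of the five weekday starts lead there under an assumed weekday schedule. The article gives no distribution of start days, so this is not a proportion of patients.

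**Conclusion.** The point holds as a minor mismatch between two stated time windows. Recording of serious adverse events closes on day 14, and the primary CT and the measurements taken with it may follow up to 3 days later. Within the window, 0 to 2 days remain after the last EMS session, and none when that session is on day 14. An event in the uncovered days falls outside the only adverse-event recording rule, in either arm.

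The 3-day maximum follows directly from the article. The day of the last session depends on the assumed placement of sessions within each week. The documents give no rate of serious events on days 15 to 17 and do not say how many assessments will fall after day 14, so neither the number of missed events nor any effect on the primary result can be estimated. It would go too far to say that the efficacy analysis is compromised. The gap lies in the completeness of the adverse-event data, and it is cheap to close.

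**What to change.** Extend the recording of serious adverse events, in both arms, through the post-intervention assessment, up to the end of day 17. State the end of the window in the same day numbering as the CT. In the same edit, reconcile it with the statement under Harms and benefits that side effects are monitored continuously during the study, so that the reader knows which period is meant.

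Asking about serious events when the function scores are collected at 1 and 2 months is optional. Nothing in the documents points to a delayed harm of EMS that would require it.

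The cost is one line in the protocol and a few case report form fields. No visit is added, because the assessment up to day 17 is already planned.

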### Participant data collection

See Fig. 1 for details of the data collection schedule. Figure 2 shows the Standard Protocol Items: Recommendations for Interventional Trials (SPIRIT) schedule for the trial protocol.Participant background: age, sex, medical history, height, weight, diagnosis at time of admission (type of trauma, AIS score, ADL, Functional Independence Measure score [8], and Barthel ADL Index [9])Physical findings for the EMS group only: blood pressure, heart rate, oxygen saturation, and level of consciousness before starting EMS, 10 min after starting EMS, and on completion of EMS; pain level using a numerical rating scale [10] during EMS; thigh and calf circumference at the time of admission (pre intervention) and on days 14–17 (post intervention); manual muscle testingImaging diagnosis: measurements of cross-sectional thigh and calf area on plain CT images taken at the time of admission (from day −  4 to day 0) and at the end of rehabilitation (days 14–17)Clinical testing: creatinine kinase (CK) level on days 0, 3, 7, and 14–17Functional Independence Measure score and Barthel ADL Index at 1 and 2 months after the injury

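### Side effects the plan promises to monitor fall under its rule against recording non-serious events, so belt-site rash and aggravated fracture-site pain leave no data unless serious

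*Protocol article*

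**What the plan says.** Four parts of the protocol article bear on this.

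- **Harms and benefits, with Potential side effects.** Of the known side effects of EMS it says that "the adverse side effects listed below have been reported, and thus will be monitored for continuously during the study". The list has three entries: skin injury and rash where the belts sit, worsening of pain at the fracture, and pain during stimulation. The only stated consequence is clinical: "If they do occur, the physician in charge will provide appropriate care and treatment".
- **Definition of adverse events.** Serious events are recorded, whatever their cause, when "occurring in the period between the date of providing informed consent and day 14". For everything else the rule is "Thus, we will not record non-serious adverse events". The reason given is that the devices are approved and in routine use.
- **Criteria for discontinuation.** Any skin or striated muscle injury ends participation. The rationale is to keep such factors from influencing the evaluation of efficacy and safety.
- **Participant data collection.** Under "Physical findings for the EMS group only" the list includes "pain level using a numerical rating scale [10] during EMS". Creatine kinase is measured on days 0, 3, 7 and 14–17.

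**The concern.** One section undertakes to watch for specific device effects, and another rules that effects of that grade will not be written down. Monitoring that leaves no record supports bedside care but produces nothing to report. An analysis plan cannot repair this later, because the data would never have been collected.

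At stake is what the trial can say about harm when it reports on benefit. If EMS preserves thigh muscle area, readers will ask what it cost the patients in skin problems and fracture pain. Fracture pain matters most here. It occurs with or without EMS, so only the randomized control group can show whether stimulation makes it worse.

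**Working it through.** No figure in the plan depends on this point, so the check is to follow each named effect through the recording rules.

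**Step 1: would the effect be serious?** The definition covers death, threat to life, hospitalization or a longer stay, lasting or significant disability, and congenital anomaly. A rash under a belt, a minor skin injury or a rise in pain would ordinarily meet none of these. An unusual case could, for example by prolonging the stay, and would then be recorded.

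**Step 2: if not serious, is it captured anywhere else?** The first entry on the list is split here because skin injury and rash are treated differently elsewhere.

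| Named effect | Captured if non-serious? | Where | Can it occur in controls? |
|---|---|---|---|
| Pain during EMS | Yes, numerical rating scale, EMS group only | Participant data collection | No, controls receive no EMS |
| Skin injury at the belt site | Indirectly at most, as a discontinuation; the article does not say that reasons are kept | Criteria for discontinuation | No, controls wear no belts |
| Rash at the belt site without skin injury | No recording stated | – | No |
| Aggravated fracture-site pain | No recording stated in either arm | – | Yes |

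**Step 3: count.** Of four effects, one is recorded directly, one may be traceable, and two leave no data unless serious.

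**Step 4: which comparison is lost?** Controls receive conventional physiotherapy alone, so three of the four effects cannot arise there and a count in the EMS group is all that is needed. The missing between-arm comparison concerns fracture-site pain only. The existing pain score does not supply it, because it is taken during stimulation and in one arm.

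**Step 5: time window.** Recording of serious events stops at day 14. The post-intervention assessment may be as late as day 17, up to 17 − 14 = 3 days later. The supervised EMS course lasts 14 days, so the window covers the whole intervention. This is a minor mismatch.

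**The case against.** The best defence is that monitoring and recording are different acts. The Harms and benefits section ties monitoring to care by the physician in charge, so both statements can be true at once. The recording rule is deliberate and reasoned. Safety is neither a primary nor a secondary endpoint, and nowhere do the authors promise a claim of clean safety. Other safety-type data are also collected: blood pressure, heart rate, oxygen saturation and consciousness around each EMS session, pain during EMS, and creatine kinase.

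Much of this stands. The two sections do not contradict each other in strict logic, and the trial does not go without safety information. What remains is that the protocol lists specific harms as worth watching and invokes an evaluation of safety when it justifies discontinuation, yet its recording rule discards two of those harms. None of the other data items stands in for rash or fracture-site pain. Nor is this detail that the article merely leaves to a fuller document: it is an explicit rule not to record.

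Three stronger readings are tempting and are not supported.

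- A reader might infer that the trial can report none of the harms it names, or that its safety result is fixed near zero in advance. Pain during EMS is scored, skin injury can surface through discontinuation, and serious events are recorded in full.
- A reader might cite the Background as saying that little is known about EMS in trauma patients. That sentence concerns efficacy, not safety.
- A reader might want to state how many events would go unrecorded. The documents give no rate for any of these effects, so any such number would be an outside assumption.

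**Conclusion.** The concern holds in limited form. The sections on harms and on adverse event recording need to be reconciled. As written, belt-site rash and aggravated fracture-site pain are captured only if serious, skin injury is visible at most through discontinuation, and fracture-site pain cannot be compared between arms.

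This rests on two assumptions. The first is that the named effects are ordinarily non-serious, which follows from the protocol's definition. The second is that the case report form, which is not shown, follows the stated rule. If the form already has fields for these effects, only the sentence in the article is wrong.

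The primary analysis of muscle area is unaffected. This is a cheap improvement to harms reporting and does not threaten the trial's main conclusion.

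**What to change.** Replace the sentence on non-serious events with a rule along these lines:

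*The effects listed under Potential side effects, and every discontinuation with its reason, are recorded on the case report form from consent through the day 14–17 assessment. Belt-site skin injury, belt-site rash and pain during EMS are recorded in the EMS arm. Pain at the fracture site is recorded in both arms, as a numerical rating score at the visits already planned. All are reported by allocated arm. Other non-serious events are not recorded.*

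This makes the recording rule match the promise to monitor. It uses the existing case report form and planned visits, and it changes no treatment or stopping rule. The comparison of fracture-site pain should be presented as descriptive: the trial is open-label, and the Discussion foresees analgesics being increased as needed, which could mask or distort a difference in scores.

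Ending the serious event window at the same day 14–17 assessment would be tidy, but it is optional.

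The cost is a few extra fields and a short pain score per patient. The reported safety profile may also look less favourable than under the present rule.

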### Confidentiality

Access to the personal information and data collected in this study will be strictly limited to investigators of this study. The data collected will be for the purpose of conducting the study only. Investigators will handle personal information carefully. The principal investigator will put in place measures for appropriate information and data handlingPhysicians in charge will initially collect data on paper. They will then register the collected data in the study database. The study database will not contain personally identifiable informationThe study database will be stored on the hard disk drive of a password-protected computer kept in a lockable room. The study group will have a key to the room and maintain security of the computer password. The study group will appropriately handle research-related printed documents, memos, and other details, for example, by viewing them in an isolated room to avoid exposure to a third party and storing them in a lockable cabinet. The study group will minimize the use of portable electronic media, but if use is absolutely necessary, members must notify the principal investigator in advance of use and handle the media with extreme cautionThe principal investigator is responsible for storage of the anonymized random number table and for supervising the format. Once data are fixed in the study database, the principal investigator will hand the random number table to the center’s planning and strategy manager and no copies will be held by the study groupPersonal information and data collected during the study will be kept for 5 years from the time of publication of the main study outcomes before disposal. Both printed and electronic materials will be destroyed so that the data are unreadable before disposal. Some writable media may be reused after overwriting the original data with dummy data to make the original data irretrievableWhen disclosing study outcomes, study members will take all due care to prevent re-identification of de-identified data

